### Outcomes

The primary outcome will be the feasibility of the intervention, measured as adherence rate, dropout rate, and the percentage of the eligible population that consented. Adherence rates will include the number of participants using TENS alone or TENS with music regularly more than once per week, adherence to filling out the pain diaries and other patient-reported outcome measures, and attendance at follow-up clinic visits.

Secondary outcomes include the following:

Pain intensity as a numerical rating scale (NRS) score collected before and after each session using a pain diary. The baseline pain will be collected for 1 week before the intervention when they initially attend the clinic.Opioid and other analgesic consumption over a 24-hour period collected in the pain diaryParticipant satisfaction using a 5-point Likert scaleMood measured through the 21-item Depression, Anxiety, and Stress ScaleFunction measured through the Patient-Specific Functional Scale [14]Compliance with other interventions, such as participation in interdisciplinary pain programsAdverse outcomes, including worsening pain and skin reaction to the electrodes used in TENS

All reported adverse reactions will also be collected through the study period when using the TENS machines through entries in the pain diary as well as during interviews with the participants. The self-reported outcome measures, such as the 21-item Depression, Anxiety, and Stress Scale and the Patient-Specific Functional Scale, will be recorded through REDCap forms during the clinic appointments. Figure 2 summarizes the process.

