### Aims

The primary aim of this study is to test the feasibility of a clinical trial comparing TENS alone to TENS combined with listening to self-selected music in participants with low-back pain with or without leg pain lasting more than 3 months. The results of this feasibility study will be used to inform a larger trial of these interventions in participants with persistent neck and low-back pain lasting more than 3 months. A larger study will be considered feasible if 80% or more of the eligible population consents to the study and 80% or more of the participants are able to adhere to the protocol. The secondary aims are to explore if combining the 2 modalities has a synergistic effect on analgesia and function. A difference of 2 points in the numerical rating scale for pain intensity will be considered significant.

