### Hypotheses

First, we hypothesize that administration of TENS combined with music will be equally feasible compared to TENS alone and will be well tolerated by participants. Second, we hypothesize that TENS combined with listening to self-selected music will have improved analgesia compared to using TENS alone.

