## Methods

### Overview

TENS with music study will be a prospective, randomized controlled pilot study to compare TENS alone to TENS combined with participant self-selected music. The participants will be randomized to receive 2 weeks of TENS therapy and 2 weeks of TENS with self-selected music using a streaming service, CD player, Long Play, or radio. The order in which this is delivered will be determined by randomization. Therefore, 1 group will receive standard TENS for 2 weeks, followed by TENS with self-selected music for 2 weeks. This order will be reversed in the other group with no washout period. The participants will be compared against themselves for the outcomes, thus reducing the number of participants to power the study. We are hoping to recruit 20 participants for this pilot trial (Figure 1). We will use TENS and TENS with music as part of a holistic pain management plan involving pain neuroscience education, behavior activation, and coping skills training that is individually tailored and not as a stand-alone intervention for pragmatic reasons.

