### Treatment

TENS will be administered for 1 hour at a time, up to a maximum of 6 times every 24 hours. Participants are free to select from available modes, which include burst, continuous, or modulate. Other parameters, such as pulse width, pulse rate, and pulse intensity, can also be modified by the participant. The pulse intensity of the TENS machine can be adjusted from 0 to 80 mA, and the pulse frequency from 2 to 150 Hz. The aim is to use the frequencies, amplitude, and mode to provide a comfortable paresthesia [13]. The participants can vary the electrode placement to provide the best possible analgesia.

The TENS will be self-administered. Music from a self-selected playlist from a set of genres such as classical, easy listening, pop, rhythm and blues, vocal, and musical will be used. We will use a participant diary to record the duration of TENS each day and the type of music listened to. Music can be listened to with or without headphones. Participants will be provided with a 1-month Spotify (Spotify AB) subscription voucher to enable ad-free music listening.

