## Discussion

### Anticipated Findings

This pilot study primarily aims to assess the feasibility of combining TENS with self-selected music. The anticipated results include approximately 80% adherence to daily use of TENS or TENS combined with self-selected music and completion of daily diaries on 80% of the study days. An adherence rate of 80% will be considered sufficient for the current data collection methods to be deemed feasible for a larger trial. It is hoped that adherence to data collection procedures, including real-time documentation of pain scores and medications used, will be evaluated among participants [15]. The trial is not likely to reveal any additive analgesic benefit for TENS and self-selected music due to the small participant numbers, but it is anticipated that a trend toward improved pain scores, better function, and reduced analgesia requirements by combining the 2 modalities may be revealed. A change of 2 points in the 11-point scale on the NRS will be most clinically relevant, but even a point difference in the NRS can be considered as the minimal clinically significant change to the participants [16]. A change in pain intensity of 2 points in the NRS is accepted as best correlated with general patient satisfaction and other meaningful outcome measures in chronic low-back pain [17]. The clinically meaningful change will differ by baseline pain; however, for pragmatic reasons in this feasibility trial, it was decided to not stratify participants based on baseline pain and adopt the general threshold. It is hoped that the acceptability of combining TENS with self-selected music as an intervention for pain management will be determined, and whether the outcome measurements and methods are perceived as burdensome and time-consuming will be assessed in this small sample. Additional insights are expected regarding noncompliance with the treatment, which may include lack of perceived improvement in pain or adverse events associated with use, such as worsening pain or skin irritation from the electrodes, as well as other factors such as lack of motivation [18].

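### Adherence is not tied to the assigned condition, so the 80% adherence criterion can be met without showing that TENS with music is feasible

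*Protocol article*

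**What the plan says.** All references are to the protocol article.

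- **Outcomes**, usage part of the primary adherence outcome: "Adherence rates will include the number of participants using TENS alone or TENS with music regularly more than once per week". The other parts are "adherence to filling out the pain diaries and other patient-reported outcome measures, and attendance at follow-up clinic visits". None of these concerns music.
- **Anticipated Findings** joins the two modes in the same way: "approximately 80% adherence to daily use of TENS or TENS combined with self-selected music".
- **Aims** sets the feasibility rule. One half is that "80% or more of the participants are able to adhere to the protocol"; the other is that "80% or more of the eligible population consents to the study". Neither half is stated by condition.
- **Hypotheses** makes a comparison between conditions: "First, we hypothesize that administration of TENS combined with music will be equally feasible compared to TENS alone". Anticipated Findings also names the feasibility of the combination as the pilot's main aim.
- **Overview** and **Randomization** give every participant two weeks of each condition in random order.
- **Treatment** summarises the diary: "We will use a participant diary to record the duration of TENS each day and the type of music listened to". The diary itself is Multimedia Appendix 1, which is not shown.

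**The concern.** In a crossover, each participant is due TENS alone in one fortnight and TENS with music in the other. Whether the combination is feasible depends on what happens in the music fortnight. The first hypothesis also needs an adherence figure for each condition, so that the two can be set side by side.

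The stated outcome provides neither. It is a single count, satisfied by either mode of use, with no reference to the period in which that use was due. A sample that takes readily to TENS but tends to skip the music could pass the adherence half of the feasibility rule. The larger trial would then be planned with no evidence that its test condition is used as intended.

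**Working it through.** **Inputs from the article:** N = 20 (Overview); adherence threshold 80% of participants (Aims), so 0.80 × 20 = 16. The article gives no expected rate of music use, so every music rate below is an assumption shown over a range. The article reports no calculation for this criterion that could be reproduced, and the sample size table is not affected.

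**Step 1: one set of data, three scorings that the text allows.** Suppose all 20 use TENS at the required frequency throughout. In the music weeks, 12 play music with it and 8 do not.

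| Scoring | Result | Against 80% |
|---|---|---|
| Either mode counts, in any period | 20/20 = 100% | met |
| Assigned treatment, pooled over person-periods | (20 + 12)/40 = 32/40 = 80% | met |
| Assigned treatment required in both periods | 12/20 = 60% | not met |

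Adherence to the combination is 12/20 = 60%, a shortfall of 100% − 60% = 40 percentage points against TENS alone. Only the third scoring reveals the failure, and the text does not require it. No single figure gives the comparison between conditions.

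A second illustration: 18 of 20 use TENS as required, but 8 of those 18 play no music in the music weeks. If either mode counts, 18/20 = 90%. For the assigned combination, (18 − 8)/20 = 10/20 = 50%.

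**Step 2: chance of meeting the adherence threshold.** Let t be the probability that a participant uses TENS at the required frequency, and m the probability that a TENS user plays music with it in the music weeks. With independent participants:

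- either mode counts: P(X ≥ 16), X ~ Binomial(20, t)
- music required in the music weeks: P(X ≥ 16), X ~ Binomial(20, t × m)

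| t (assumed) | Either mode counts, any m | Music required, m = 100% | m = 90% | m = 75% | m = 50% | m = 0% |
|---|---|---|---|---|---|---|
| 80% | 0.63 | 0.63 | 0.30 | 0.05 | 0.0003 | 0 |
| 85% | 0.83 | 0.83 | 0.48 | 0.10 | 0.0007 | 0 |
| 90% | 0.96 | 0.96 | 0.67 | 0.17 | 0.002 | 0 |
| 95% | 0.997 | 0.997 | 0.85 | 0.28 | 0.003 | 0 |

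For example, t = 90% and m = 75% give t × m = 0.675 and P(X ≥ 16) = 0.17. When either mode counts, m does not enter the calculation, so that scoring carries no information about music use.

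**The case against.** The strongest reply is that *or* simply names the two crossover conditions, so that each participant is judged on whichever is assigned. Aims supports this: it asks for adherence to the protocol, and the protocol assigns music for two weeks. Nothing in the article says outright that TENS without music in the music weeks counts as adherent. This stands to the extent that the wording permits such counting but does not mandate it. It does not remove the problem, because a rate pooled over periods can still reach 80% while the music weeks fail (32/40 in Step 1).

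It can also be said that adherence by condition could be tabulated from the daily diaries, since the assigned condition is known for each week. That is true, and it means the first hypothesis is not beyond reach. But the article does not name that tabulation as the outcome or attach the threshold to it.

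A reader might infer four stronger things that the documents do not support.

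- *The larger trial could proceed on TENS adherence alone.* Aims also requires 80% consent, and the abstract's Conclusions and Future Directions add a positive trend for the combination.
- *The per-protocol set would contain people who never received the test condition.* Statistical Methods does not define that set, and its definition is commonly left to the analysis plan.
- *The diary cannot show whether music was played.* The form is not shown. Outcomes has pain recorded before and after each session, so part of the diary is at session level, and a record of music type might reveal complete non-use.
- *Radio listening should not count as self-selected music.* Overview lists radio among the permitted sources, and a listener can choose a station.

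**Conclusion.** The point holds as a defect of definition. The primary adherence outcome and its single 80% threshold are not specific to the combination, although the first hypothesis and the stated main aim are. Passing the adherence half of the feasibility rule would not show that TENS with music is feasible, or as feasible as TENS alone.

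The possible effect on the decision is large. Data with 60% adherence in the music weeks can be scored as 100%, 80% or 60%, depending on how the sentence is read. At an assumed 90% TENS use and 75% music use among TENS users, the chance of meeting the threshold is 0.96 or 0.17 according to the scoring. These figures rest on assumed usage rates and independent participants. If nearly everyone plays music when it is due, the scorings agree and nothing is lost. The point is best treated as a cheap improvement.

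**What to change.** 1. Reword Outcomes so that adherence is scored separately by assigned condition. In the music weeks, count use only when music accompanies TENS.
2. Apply the 80% criterion in Aims to the TENS-with-music weeks, and bring the wording in Anticipated Findings into line.
3. For the first hypothesis, report the within-participant difference in adherence between conditions with a 95% CI suited to paired proportions. This fits the descriptive approach already planned in Statistical Methods.
4. Confirm that the diary records whether music accompanied each session, and add a yes/no field if it does not.

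The cost is a few sentences and at most one diary field. Reported adherence may be lower, and diary burden may rise slightly, which matters because Limitations already names that burden. Scoring by assigned condition needs the sequence, and Blinding keeps the data collator and statistician unaware of it, so the rule should say who links the two. Results reports 4 of 20 participants enrolled at submission, so a change made early would cover most of the sample.

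### Adherent use is more than once a week in Outcomes but daily in the Discussion, so the 80% feasibility rule can give opposite answers from the same diaries

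*Protocol article*

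**What the plan says.** The feasibility rule is in the Aims and has two conditions. The first is consent: "A larger study will be considered feasible if 80% or more of the eligible population consents to the study". The second is adherence: "80% or more of the participants are able to adhere to the protocol". The Aims do not say what adhering means.

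Outcomes makes the adherence rate part of the primary outcome and describes it through several components. The use component is "the number of participants using TENS alone or TENS with music regularly more than once per week". The others are "adherence to filling out the pain diaries and other patient-reported outcome measures, and attendance at follow-up clinic visits".

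The Discussion (Anticipated Findings) describes use differently. It expects "approximately 80% adherence to daily use of TENS or TENS combined with self-selected music", together with "completion of daily diaries on 80% of the study days". The next sentence reads: "An adherence rate of 80% will be considered sufficient for the current data collection methods to be deemed feasible for a larger trial". Later, the Discussion reports that adherence in TENS trials ranges from 50% to 80% and says the higher figure was chosen.

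Treatment gives a ceiling of six one-hour sessions in 24 hours and no minimum. It also says the diary records each day's TENS duration and the type of music. The first hypothesis is that "TENS combined with music will be equally feasible compared to TENS alone".

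**The concern.** Adherence is half of the rule that decides whether a larger trial goes ahead. More than once a week and daily are far apart, and many participants could fall between them. Treatment prescribes no minimum use, so adhering to the protocol cannot be read off the treatment schedule either.

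If the definition is still open when the diaries come in, it can be picked with the results in view. A pattern of moderate use could then be reported as clear success or clear failure.

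A smaller matter is that the use component names both treatments in one phrase and does not ask for a rate in each period. The first hypothesis compares the two treatments on feasibility, so a rate per period is what it needs.

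**Working it through.** The plan gives no figure for this point, so there is nothing to reproduce. The check applies each wording to the same diary data.

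**Inputs**
- Participants: 20 (Methods, Overview).
- Treatment time: 2 + 2 weeks = 28 days (Methods, Overview).
- Threshold: 80% of participants (Aims), so 0.8 × 20 = 16 participants.
- Outcomes rule: more than once a week, taken as at least 2 use-days in each of the 4 weeks.
- Discussion, one reading: use on at least 80% of days. 0.8 × 28 = 22.4, so at least 23 of 28 days.

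**Step 1: fixed patterns, no probability model.** Suppose all 20 participants use TENS on k days every week.

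| k days/week | Days of 28 | Outcomes rule | At least 23 of 28 days |
|---|---|---|---|
| 2 | 8 (29%) | 20/20 | 0/20 |
| 3 | 12 (43%) | 20/20 | 0/20 |
| 4 | 16 (57%) | 20/20 | 0/20 |
| 5 | 20 (71%) | 20/20 | 0/20 |
| 6 | 24 (86%) | 20/20 | 20/20 |
| 7 | 28 (100%) | 20/20 | 20/20 |

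From 2 to 5 days a week the two columns lead to opposite decisions.

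**Step 2: other readings of daily use.** If daily means every day, 6 days a week also fails and the gap widens. If the 80% is a share of all participant-days, the rates for 2 to 5 days a week are 29% to 71%, all below 80%. So the split over 2 to 5 days does not depend on which of these readings is taken. It disappears only if the daily-use wording is treated purely as a forecast.

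**Step 3: illustration with variable use.** Assume that each participant uses TENS on any day with probability q, independently between days and participants, with at most one counted use per day. The values of q are assumptions.
- Outcomes rule: W(q) = [1 − (1−q)^7 − 7q(1−q)^6]^4. At q = 0.6 this is [1 − 0.0016 − 0.0172]^4 = 0.9812^4 = 0.927.
- 23-of-28 reading: D(q) = P(Binomial(28, q) ≥ 23).
- Threshold met: P(Binomial(20, W or D) ≥ 16).

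| q | W | D | Threshold met under W | Threshold met under D |
|---|---|---|---|---|
| 0.5 | 0.772 | 0.0005 | 0.51 | 0.00 |
| 0.6 | 0.927 | 0.011 | 0.99 | 0.00 |
| 0.7 | 0.985 | 0.113 | 1.00 | 0.00 |
| 0.8 | 0.999 | 0.501 | 1.00 | 0.01 |
| 0.85 | 1.000 | 0.765 | 1.00 | 0.48 |
| 0.9 | 1.000 | 0.945 | 1.00 | 1.00 |

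Under these assumptions the two wordings part company from about q = 0.5 and agree again by q = 0.9.

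**The case against.** The strongest reply is that there is only one operative definition, the one in Outcomes. The daily-use text stands under Anticipated Findings and is worded as an expected result, and expecting more than the minimum does not redefine an endpoint. The 80% sentence that follows concerns data collection methods, comes straight after the diary expectation, and may refer only to diaries. On that view a diary criterion counted in days and a use criterion counted in participants are two components, and there is no conflict of units.

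Much of this stands. A reader might infer that the plan contains two formal, rival decision rules for use. The documents do not go that far: daily use is anticipated, and the 80%-of-days figure belongs to diary completion. The 23-of-28 rule for use is a reading of the text, and so are the probabilities built on it.

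A reader might also infer that naming both treatments in one phrase makes the first hypothesis untestable. It does not. Each treatment has its own two-week period, and the diary records daily TENS duration and music type, so adherence by period can be computed. The phrase may simply mean whichever treatment is assigned at the time.

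The reply does not remove the inconsistency. The 80% sentence uses the language of a criterion, speaks of an adherence rate without limiting it to diaries, and follows directly on a sentence about daily use. The Aims leave adherence undefined, and no section says which frequency the rule uses. This is a conflict between stated frequencies, so it is more than detail left to a fuller document.

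**Conclusion.** The point holds as an inconsistency in the use frequency behind the adherence half of the feasibility rule. With steady use on 2 to 5 days a week by all 20 participants, the result is 20/20 under Outcomes and 0/20 under the 23-of-28-day reading of the Discussion, against a threshold of 16. The fixed-pattern result needs no probability model. It does need the Discussion's daily use to be taken as the standard for adherence, which the text permits but does not state outright. The binomial figures also rest on independent days, a common q and one counted use per day, and serve only to show that the disagreement covers a wide range of use.

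Reporting by period is an improvement that the first hypothesis calls for. The existing data can already answer that hypothesis.

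**What to change.** Before the diaries are analysed:

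1. Reconcile the Aims, Outcomes and Anticipated Findings into one participant-level definition of adherent use. The sponsor chooses the frequency. State in the Aims that the 80% rule uses this definition, and align the Discussion with it.
2. State the diary criterion, 80% of study days, as a separate component with its own unit, so that it cannot be taken for a rule about use.
3. Report adherence separately for the TENS-alone and TENS-with-music periods, with the within-participant difference and a confidence interval. Say that a participant who stops the music does not count as adherent to TENS with music.

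The cost is wording and a small amount of extra analysis, since the diary already collects what is needed. Four participants were enrolled at submission against a target of 20, so the change can still be made before results are known. The drawback is that, if the stricter frequency is retained, 80% may be harder to reach.

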**Figure 2. F2:**
[figure not shown]
Workflow for transcutaneous electrical nerve stimulation with music pilot study. DASS-21: 21-item Depression, Anxiety, and Stress Scale; PSFS: Patient-Specific Functional Scale.

### Blinding

The observer who collates the data and the statistician who analyzes the results will be blinded. The participants will not be blinded, as blinding is not pragmatic for this intervention. The equipment required includes a TENS machine, a pain diary, and the participants’ own device for listening to music on Spotify, CD, LP, radio, or other music listening devices.

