### Randomization

Participants will be randomized in a 1:1 ratio to 1 of 2 treatment sequences:

Sequence AB: 2 weeks of standard TENS followed by 2 weeks of TENS combined with self-selected musicSequence BA: 2 weeks of TENS combined with self-selected music followed by 2 weeks of standard TENS

Randomization will be performed using a computer-generated allocation list created in Stata (StataCorp LLC) before study commencement. A permuted block design with variable block sizes will be used to ensure balance between sequences throughout recruitment. The randomization seed and code will be archived to allow reproducibility. Allocation concealment will be maintained by storing the randomization list in the Research Electronic Data Capture (REDCap; Vanderbilt University) randomization module, which will reveal the assigned sequence only after a participant has provided informed consent and completed baseline assessments.

The randomization result will be communicated to participants by telephone within 24 hours of their initial assessment. Investigators responsible for outcome collection and statistical analysis will remain blinded to treatment sequence. Participants cannot be blinded due to the pragmatic nature of the intervention.

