### Data Collection

A standardized pain diary (Multimedia Appendix 1) will be used for collecting the primary outcome and some of the secondary outcomes, such as medication taken over 24 hours. Specific forms will be used for other secondary outcomes, which are available through REDCap. The data will be stored in a password-protected, secure database via REDCap. The data collected will be deidentified and assigned a study code. The pain management unit will be the custodian of the data stored in the password-protected drive within the local health district computer, with access restricted to the investigators only. The data will be stored for 7 years after the completion of the study. Table 1 summarizes the data collection points.

**Table 1. T1:** Data collection points.

Measure	Frequency	Collection points
Pain diaries	Daily	Baseline, week 1, week 2, week 3, and week 4
Average pain over 24 hours (numerical rating scale)	Weekly	Baseline, week 1, week 2, week 3, and week 4
Medications	Weekly	Baseline, week 1, week 2, week 3, and week 4
Patient-Specific Functional Scale	Fortnightly	Baseline, week 2, and week 4
21-item Depression, Anxiety, and Stress Scale	Fortnightly	Baseline, week 2, and week 4
Pain sites update	1 time	Baseline
Pain duration	1 time	Baseline
Demographics	1 time	Baseline

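### The blinding to sequence claimed for outcome collectors and the data collator cannot be maintained as described, because the outcome diary records the music; the statistician's blinding is not contradicted.

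*Protocol article*

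**What the plan says.** Two sections of the protocol article claim blinding beyond the statistician.

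- Blinding: "The observer who collates the data and the statistician who analyzes the results will be blinded".
- Randomization: "Investigators responsible for outcome collection and statistical analysis will remain blinded to treatment sequence".

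Other sections describe what those people work with.

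- Treatment: "We will use a participant diary to record the duration of TENS each day and the type of music listened to".
- Data Collection: "A standardized pain diary (Multimedia Appendix 1) will be used for collecting the primary outcome and some of the secondary outcomes".
- Outcomes, on pain: "Pain intensity as a numerical rating scale (NRS) score collected before and after each session using a pain diary". The same section takes analgesic consumption from the diary, and adverse reactions from the diary and from participant interviews.
- Outcomes, on adherence: "Adherence rates will include the number of participants using TENS alone or TENS with music regularly more than once per week".

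Participants are openly unblinded (Randomization, Blinding, Limitations). Data are deidentified and given a study code (Data Collection). The DASS-21 and the Patient-Specific Functional Scale are completed on REDCap forms at clinic appointments (Outcomes).

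**The concern.** The people said to be blinded to sequence are those who collect and collate outcomes, and the main instrument for those outcomes records the one feature that separates the two conditions. Someone who reads a diary with music entries in one fortnight and none in the other knows the order of treatment.

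Two things are at stake. The trial report would credit the study with blinded outcome collection that its procedures do not deliver, and the planners of the larger trial might carry the claim forward. In addition, some items call for staff judgement: whether a participant used TENS with music regularly, how an adverse reaction mentioned in an interview is recorded, and who belongs in the per-protocol set. Knowledge of condition could influence these.

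**Working it through.** No sample size, power or error rate is involved, so the check sets the sections side by side.

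1. **What is claimed.** Randomization names the object of blinding (treatment sequence) and the people (those who collect outcomes and those who analyse). Blinding names the collating observer and the statistician.

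2. **What the diary shows.** Under Treatment, the diary records music type. Under Data Collection and Outcomes, a diary supplies adherence, session pain, 24-hour analgesic use and some adverse reactions. Collating these outcomes therefore means working from the diary.

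3. **Does a music entry reveal the sequence?** Randomization defines two sequences of two fortnights each:

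| Music entries seen in | Sequence |
|---|---|
| Weeks 3–4 | AB |
| Weeks 1–2 | BA |

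The mapping is one to one, so music entries confined to one fortnight identify the sequence.

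4. **Is there a masking step?** The article describes none. Deidentification and a study code conceal who the participant is, not which condition applied.

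5. **Other routes.** Adverse reactions are also collected in interviews, where the participant knows the condition and can disclose it. Per-protocol analyses are planned (Statistical Methods), and deciding whether someone followed the assigned condition plausibly needs the sequence and the music entries.

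6. **Which outcomes are exposed?**

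| Item | Needs or reveals the condition? |
|---|---|
| Consent percentage, dropout | No |
| Diary completion, questionnaire completion, visit attendance | The count itself does not need it |
| Regular use of TENS alone or with music | Yes, if counted by condition |
| Session pain, analgesic use | Diary reveals it, but the participant supplies the value |
| DASS-21, Patient-Specific Functional Scale | Separate forms that do not record music |
| Adverse reactions from interviews | Can reveal it |
| Per-protocol membership | Plausibly needs it |

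On regular use, Outcomes counts "the number of participants using TENS alone or TENS with music regularly more than once per week". That can be read as one combined count or one count per condition. The hypothesis that "administration of TENS combined with music will be equally feasible compared to TENS alone" favours the second reading but does not settle it.

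7. **Scale of the adherence rule.** Aims sets feasibility at 80% or more of participants adhering. With the target of 20, that is 0.80 × 20 = 16 participants, and each is worth 1/20 = 5 percentage points. A single classification could matter if the count fell at the boundary. This shows the sensitivity of the rule; it is not evidence of bias.

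8. **The statistician.** Nothing in the article requires the analyst to see music entries for the main analyses. The mixed model needs treatment, period and sequence, and each can be supplied under neutral codes.

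**The case against.** The strongest case on the other side has four parts.

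- **Who sees what is inferred.** No sentence says that the blinded observer reads diaries with the music entries visible, or who holds the interviews. The diary form (Multimedia Appendix 1), the workflow figure and the full protocol are not shown, and an article may leave such operational detail to them. This stands as a limit on certainty: no proportion of unblinded diaries can be given. It does not remove the conflict between the printed blinding claims and the printed diary content.
- **Much is untouched.** The statistician can work from coded data, the mood and function forms do not record music, and most feasibility components need no knowledge of condition. This stands in full. A reader might infer that the trial has no blinding at all, or that the primary outcome cannot be scored without unblinding. The document supports neither.
- **The impact is small.** Pain, mood, function and satisfaction are reported by participants whose lack of blinding is disclosed, so masking a collator would not remove the main reporting bias. Feasibility is analysed descriptively, and use more than once per week is a simple threshold. This largely stands. Some room for judgement remains, because Anticipated Findings refers to daily use where Outcomes sets the weekly threshold.
- **Redesigning the diary would be a poor remedy.** Future Directions says the pilot tests the diaries as an instrument, Limitations already names recording burden, and 4 participants were enrolled at submission. This stands: a separate music log would change the instrument mid-trial and add burden, so it is not recommended.

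**Conclusion.** The point holds in a limited form. The article claims blinding to sequence for outcome collectors and the data collator, and its own description of the diary and the interviews does not allow that to be maintained. The statistician's blinding is not contradicted.

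The size of any bias cannot be calculated from the document. It is expected to be small for self-reported pain, mood and function. The exposure is confined to judged items: classification of TENS-with-music use, interview-based adverse reactions and per-protocol membership. No bias in the feasibility decision has been shown.

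The conclusion assumes that the people who collect or collate outcomes see the diary's music entries. That is a strong inference from Blinding, Treatment and Data Collection taken together, but it is not stated. If the full protocol contains a masking step, the correction is to describe it in these sections.

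**What to change.** Restate the sentences under Randomization and Blinding so that they say who is blinded, to what and how:

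- Claim blinding only for the statistician. The statistician receives data with treatment coded X/Y and no music fields until the main pain, mood, function and medication analyses are final. The code and the music fields are released after that, before the per-protocol analyses.
- State that staff who handle diaries, classify use by condition or hold interviews are not blinded.

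The cost is a less favourable blinding statement and a small data-coding step. No diary redesign or extra form is needed, so nothing changes for participants already enrolled.
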